**Surgical treatment of type II DM**

Recently, metabolic surgery has attracted attention as a new treatment method for a treatment of type 2 diabetes. Metabolic surgery was first introduced for the treatment of metabolic diseases such as hyperglycemia, as it was reported that the hyperglycemia of obese patients was improved as a result of surgery to reduce the body weight of obese patients.

Metabolic surgery is a surgical procedure that changes the pathways of food in gastrointestinal track. As laparoscopic surgery, which showed its’ benefit of less scar and early recovery from surgery, is introduced for metabolic surgery, attention to metabolic surgery have been accelerated. Adjustable gastric banding (AGB), Roux-en-Y gastric bypass (RYGB), biliopancreatic diversion (BPD) are the name of metabolic surgery, and RYGB and BPD are preferred procedure to control hyperglycemia.

RYGB is one of the common metabolic surgery procedures: After making small amount of gastric pouch, jejunum is resected 30-50 cm below treiz ligament and do RY anastomosis with 50-150 cm of Rou limb.

[figure not shown]

It was reported that eighty percent of hyperglycemia patients who underwent this surgery, experienced reduction of the amount of insulin hypoglycemic drug and insulin. Also this surgery was effective even patients with less than 35 kg/m^2^ of body mass index.

**The mechanism of improving diabetes by surgery**

Basically reducing oral intake and nutritional absorption in GI track is a mechanism of improving hyperglycemia by surgery. In addition, various hormones such as GLP-1, IGF-1, Leptin, CCK, Ghrelin, Neuropeptide Y, which is changed its level bypassing food can lead the improvement of impairment of insulin and hyperglycemia.

1. **The upper intestinal hypothesis**

There is a theory for the improvement of hyperglycemia for patients receiving metabolic surgery: if food does not pass through duodenum (food does not contact any upper GI mucosa), an unknown-hormone which related insulin resistance, is not secreted, consequently, it can improve hyperglycemia. A study showed that duodeno-jejunal bypass (DJB) could improve DM without notable weight loss or the amount of diet. Also another study showed that excluding duodenum for food passage led improving DM, but re-including duodenum led recurrence of DM. Another study which can valid this theory showed that endoluminal duodenal sleeve which prevent the contact between duodenal mucosa and food lead improving DM.

[figure not shown]

Proximal bowel hypothesis: When excluding proximal bowel including duodenum for food passage lead improving DM (Rubino et al. Ann Surg, 2008)

1. **The lower intestinal hypothesis**

RYGB and BPD procedure makes early contacting food to distal small bowel and it lead secretion of GLP-1, one of incretin peptide and this mechanism would be related to improving DM. GLP-1 induces glucose-dependent insulin secretion and inhibits glucagon secretion, and delays gastric empting. Also, it induced increasing mass of beta-cell in *in vivo* model. GLP-1 is stimulated by nutritional contacting at L-cell in ileum and colon and induces inhibition of appetite and reducing glucose level.

[figure not shown]

Distal bowel hypothesis: early contacting food to distal part of small bowel lead secretion of GLP-1 in L-cell and it stimulate the effect of glucagon. (Rubino et al. Ann Surg. 2008)

1. **The ghrelin hypothesis**

Ghrelin stimulate appetite and is a hormone related in impairment of DM control. It is increased just before diet and decreased after diet. Over 90% of Ghrelin is secreted at stomach and duodenum, and RYGB makes food bypassing stomach and duodenum, consequently this procedure would prevent secretion of ghrelin. It was reported that RYGB was related to low level of ghrelin. Because ghrelin inhibits adiponectin, one of hormone of insulin-sensitizing hormone, and block phosphatidylinositol-3-kinase signal in liver, reducing ghrelin level by RYGB would induce the control of DM.

**Surgical treatment for patients with gastric cancer and type II DM.**

Gastrectomy for gastric cancer leads weight loss of patient and sometimes the patient experience resolution of co-morbidity such as hypertension and DM. Therefore, modifying gastric cancer surgery with adaption of metabolic surgery could improve DM more efficiently. The main procedure for gastric cancer surgery is that resection of stomach including cancer and lymph node dissection. The extent of gastrectomy is decided not by the presence of DM but by location of tumor and surgeon’s preferences; gastroduodenostomy, gastrojejunostomy with loop type, and Roux-en-Y gastrojejunostomy are the common reconstruction type. The type of reconstruction is known that it is not related to the patients’ prognosis. Recent study reported that subtotal gastrectomy with Roux-en-Y reconstruction for gastric cancer was related improvement of DM; 57% of patients were not required any medication for DM at 1 year after gastrectomy. Thus, this study is going to compare the outcome of DM improvement after subtotal gastrectomy for patients with gastric cancer and DM between Roux-en-Y gastrojejunostomy and gastroduodenostomy.

[figure not shown]

[figure not shown]

(Roux-en-Y gastrojejunostomy) (Gastroduodenostomy)

# Roux-en-Y gastrojejunostomy

Transecting jejunum was performed 25-30cm below treiz ligament after standard gastrectomy with lymphadenectomy. Side-to side jejuno-jejunostomy was performed 30-40cm below gastrojejunostomy.

# Gastroduodenostomy

Gastroduodenostomy was performed using circular staple and the common channel was repaired by linear stapler after standard gastrectomy with lymphadenectomy.

Until now, no randomized controlled trial has been conducted for comparing the efficacy of DM improvement according to reconstruction type for gastric cancer surgery.

1. **Purpose**
2. Comparing the effect of improvement of hyperglycemia according to reconstruction type (Roux-en-Y gastrojejunostomy vs. gastroduodenostomy) in patients with gastric cancer and DM
3. Evaluating the mechanism of DM improvement according to reconstruction type.
4. **Place and period of the study**

Place: Severance hospital, Yonsei University College of Medicine

Periods: 2011.05.01~2014.04.30 (36 months)

1. **Selection criteria**

Inclusion criteria

1. Plan to underwent surgery for early gastric cancer, and in treatment for diagnosed DM and/or newly diagnosed DM in pre-operative check up
2. Location of tumor is lower part of stomach (possible cases of distal gastrectomy)
3. Age between 20-80
4. Understand the study and informed consent patients

Exclusion criteria

1. Patients who were treated by systemic inflammatory disease or with other malignancy
2. Uncontrolled co-morbidity
3. Vulnerable subjects (minor, pregnant women, lack of ability of recognition)
4. Severe complication after gastrectomy
5. **Sample size**

Retrospective study from our institution showed that proportion of patients who experience complete remission of DM, which was defined as no more necessity drug to control DM, was around 15% after gastroduodenostomy. It was reported that around 57% of patients who underwent Roux-en-Y gastrojejunostomy for gastric cancer with DM experienced remission of DM. Thus sample size for each group will be 18 for 0.05 of alpha and 0.20 of beta, and estimating 10% of drop-out rate, total 40 patients will be required.

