**<Methods>**

- Selecting patients who satisfy inclusion and exclusion criteria
- Randomization (without blinding):
  - Experiment arm: Roux-en-Y gastrojejunostomy
  - Control arm: Gastroduodenostomy
- Laboratory follow up: preoperation, post-operative day#7, #3months, #12 months
- Weight, fasting sugar level, post prandial 2hr sugar level, HbA1c, C-peptide (both of fasting and post prandial 2hr), lipid profile, insulin (both of fasting and post prandial 2hr), glucagon, IGF-1, GLP-1, Neuropeptide Y, Ghrelin, Leptin
- HOMA scale: HI=plasma glucose(mmol.L) x insulin(UI/ml)/22.5
- Comparing the outcomes between Roux-en-Y gastrojejunostomy and Gastroduodenostomy

1. **Variables**

-height, weight

-blood pressure, pulse rate

-duration of DM, duration of DM treatment, drug for DM

-insulin or not and amount

-pathology, postoperative morbidity and mortality

-Weight, fasting sugar level, post prandial 2hr sugar level, HbA1c, C-peptide (both of fasting and post prandial 2hr), lipid profile, insulin (both of fasting and post prandial 2hr), glucagon, IGF-1, GLP-1, Neuropeptide Y, Ghrelin, Leptin

- Laboratory follow up: preoperation, post-operative day#7, #3months, #12 months

-questionaire for quality of life

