***Evaluation of hormonal change**

(1) blood sampling and centrifuge for plasma

Sampling at follow up point

Keep 8hr of NPO, storage in EDTA tube, centrifuge at 4℃, 1600 x g for 15 minutes. Keep plasma at -70℃

(2) Radioimmunoassay (RIA)

<commercial RIA kits>

Ghrelin과 Leptin (Linco Research, St. Charles, Missouri)

GLP-1과 NPY (Interscience Institute, Inglewood, CA)

Glucagon, IGF-1 (Endocrine Sciences Inc., Calabasas, CA)

1. **Estimated side effects of this study**

No specific additional risk

Same as standard gastrectomy

1. **Trial drop-out and stop**

When participant withdraw his/her agreement

1. **Analysis and interpretation**

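### Exclusion criterion 4 (severe complication after gastrectomy) can only take effect after randomisation, so it removes randomised patients on an open-label judgement and can bias the comparison in either direction

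*Protocol*

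**What the plan says.** In the Protocol, Selection criteria, the fourth exclusion criterion is "Severe complication after gastrectomy". The first inclusion criterion describes a patient who has not yet been operated on: "Plan to underwent surgery for early gastric cancer".

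Under <Methods>, the first step is "Selecting patients who satisfy inclusion and exclusion criteria". The next is "Randomization (without blinding"), which assigns Roux-en-Y gastrojejunostomy or gastroduodenostomy. The section on the Roux-en-Y technique places the reconstruction directly after the resection in one operation: "Transecting jejunum was performed 25-30cm below treiz ligament after standard gastrectomy with lymphadenectomy". The gastroduodenostomy section does the same for the control arm.

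Three other places bear on the point:
- Variables lists "pathology, postoperative morbidity and mortality" among the data to be collected.
- Trial drop-out and stop gives one reason only: "When participant withdraw his/her agreement".
- The section on safety criteria states that no reporting of postoperative complications is planned.

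Sample size adds a loss allowance to 18 per arm: "estimating 10% of drop-out rate, total 40 patients will be required".

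**The concern.** An eligibility criterion should rest on what is known before allocation. This one rests on a consequence of the operation whose reconstruction is being randomised. If it is applied as written, the groups compared are those who came through surgery without a severe complication, not those who were randomised.

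Three features make this more than a formality. The two reconstructions differ surgically: Roux-en-Y has a gastrojejunostomy and a jejuno-jejunostomy, the control a single gastroduodenostomy, so complication rates may depend on the arm. The protocol gives no grade, definition or time window for severity. Whoever makes the judgement knows the allocation. With about 20 patients per arm, a few such removals can shift the remission comparison and reduce the evaluable number.

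**Working it through.** **1. Timing.** Selection takes place while surgery is planned. Randomisation follows selection. The exact moment of randomisation is not stated, but it assigns the reconstruction and so must precede it. A complication after gastrectomy follows the resection and the reconstruction. The order is therefore selection, randomisation, resection with the allocated reconstruction, complication. Criterion 4 can screen out nobody at entry. This step needs no assumed figure.

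**2. The plan's own figures.** Inputs from Sample size and the power output: 57% versus 15%, 18 per arm, two-sided likelihood ratio test, target alpha 0.05. Summing exact binomial probabilities over all outcomes with a likelihood ratio statistic of at least 3.841 gives power 0.8091 and actual alpha 0.0764, as printed. The total is 36 / (1 − 0.10) = 40, also as printed. The chi-square test named under Statistical analysis gives exact power 0.794 at 18 per arm.

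**3. Effect on the estimate (illustration).** Assumptions, none of them from the documents: the planning rates hold among uncomplicated patients, severe complications occur in 15% of the Roux-en-Y arm and 5% of the control arm, and a share r of complicated patients remits in either arm.

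- With complicated patients excluded: 0.57 − 0.15 = 0.42.
- All randomised, Roux-en-Y: 0.85 × 0.57 + 0.15r = 0.4845 + 0.15r.
- All randomised, control: 0.95 × 0.15 + 0.05r = 0.1425 + 0.05r.
- Difference: 0.342 + 0.10r.

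| Complicated patients who remit | All-randomised difference | Difference after exclusion |
|---|---|---|
| none (r = 0) | 34.2 points | 42 points |
| half (r = 0.5) | 39.2 points | 42 points |
| all (r = 1) | 44.2 points | 42 points |

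Exclusion overstates the difference in the first two rows and understates it in the third.

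**4. The same check under no true effect.** Assume 35% remission in both arms overall and complications of 20% versus 5%. After exclusion:

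- none of the complicated remit: 0.35/0.80 − 0.35/0.95 = 0.437 − 0.368 = +6.9 points;
- all of them remit: (0.35 − 0.20)/0.80 − (0.35 − 0.05)/0.95 = 0.187 − 0.316 = −12.8 points.

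With equal complication rates, and equal remission among the complicated, this spurious difference is zero.

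**5. Effect on numbers (illustration).** The 10% allowance is 40 − 36 = 4 patients. If four more were excluded for complications, 32 would remain. At 16 per arm, exact power for 57% versus 15% is 0.743 by either test, against 0.794 (chi-square) or 0.809 (likelihood ratio) at 18 per arm. The loss is about 5 points on chi-square or 7 on the likelihood ratio test.

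**The case against.** Several objections carry weight.

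- **Direction.** A reader might infer that the rule flatters whichever arm has more complications. That follows only if complicated patients remit less often. The protocol does not say so, and its background section links weight loss after gastrectomy to resolution of diabetes, so the opposite is possible. The inference is not supported.
- **Differential rates.** The protocol gives no complication rate. It says that reconstruction type is unrelated to prognosis and that the expected risks are those of standard gastrectomy. This does not establish equal complication rates, but it does mean that the 15% versus 5% used above is purely illustrative.
- **Hidden harms.** A reader might infer that the criterion makes harms vanish from the trial. It does not do so by itself, since morbidity and mortality are collected variables. The gap in reporting comes from the safety section.
- **Power.** Setting 74% by chi-square against the printed 81% mixes two tests. The protocol also does not say what its 10% covers, so complication exclusions may already be inside it.
- **Application.** Consent withdrawal is the only stated reason for drop-out, so whether criterion 4 ends follow-up or removes patients from the analysis is not spelled out. Removal is the natural reading of an exclusion criterion, but it remains a reading.
- **An earlier gastrectomy.** The line might refer to previous surgery. Nothing in its wording says so, and the patients are awaiting distal gastrectomy for early cancer. If that was meant, the line still needs rewriting.

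These points limit what can be said about size and direction. They do not touch the timing contradiction, and nothing in the protocol keeps such patients in the comparison. Leaving the matter to an analysis plan would not resolve it, because a plan that analysed all randomised patients would contradict the stated criterion.

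**Conclusion.** The point holds as a defect in a stated rule. Criterion 4 can act only after allocation, on an undefined and unblinded judgement, for an event that the allocated reconstruction may influence. It should be corrected, because it undermines the randomised comparison in a 40-patient trial.

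The bias arises if complications differ by arm and are related to remission, and it can go either way. Under the assumed 15% versus 5% complication rates, the reported 42 points stands against a true all-randomised difference anywhere from 34 to 44. The fall in power to about 0.74 is conditional on four exclusions beyond the drop-out allowance. None of these sizes can be taken as a prediction, and the conclusion does not depend on them.

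**What to change.** 1. Delete criterion 4 from the eligibility criteria.
2. State that every randomised patient is analysed in the assigned arm, with remission status at 12 months as observed, including patients with severe complications.
3. Define severe complication and report it by arm from the morbidity and mortality data already collected. Reconcile this with the safety section, which plans no such reporting.
4. Show results without these patients only as a labelled sensitivity analysis.

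The cost is a short amendment, with no new data to collect. It may also cost power: if complicated patients remit less often, the all-randomised effect is smaller than the one planned for. In the none-remit scenario (48.45% versus 14.25%), exact power at 18 per arm is about 0.62 by chi-square or 0.66 by likelihood ratio. If the sponsor considers that scenario realistic, the sample size should be reviewed in the same amendment.

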# **Two Independent Proportions (Null Case) Power Analysis**

**Numeric Results of Tests Based on the Difference: P1 - P2**

**H0: P1-P2=0. H1: P1-P2=D1<>0. Test Statistic: Likelihood Ratio test**

**Sample Sample Prop|H1 Prop**

**Size Size Grp 1 or Grp 2 or Diff Diff**

**Grp 1 Grp 2 Trtmnt Control if H0 if H1 Target Actual**

**Power N1 N2 P1 P2 D0 D1 Alpha Alpha Beta**

0.8091 18 18 0.5700 0.1500 0.0000 0.4200 0.0500 0.0764 0.1909

Note: exact results based on the binomial were only calculated when both N1 and N2 were less than 100.

**Report Definitions**

'Power' is the probability of rejecting a false null hypothesis. It should be close to one.

'N1 and N2' are the sizes of the samples drawn from the corresponding populations.

'P1' is the proportion for group one under H1. This is the treatment or experimental group.

'P2' is the proportion for group two. This is the standard, reference, or control group

'Target Alpha' is the probability of rejecting a true null hypothesis that was desired.

'Actual Alpha' is the value of alpha that is actually achieved.

'Beta' is the probability of accepting a false null hypothesis.

**Summary Statements**

Group sample sizes of 18 in group one and 18 in group two achieve 81% power to detect a difference between the group proportions of 0.4200. The proportion in group one (the treatment group) is assumed to be 0.1500 under the null hypothesis and 0.5700 under the alternative hypothesis. The proportion in group two (the control group) is 0.1500. The test statistic used is the two-sided Likelihood Ratio test. The significance level of the test was targeted at 0.0500. The significance level actually achieved by this design is 0.0764.

The formula for estimation was like as follow:

[figure not shown]

In our institution, around 50 patients underwent subtotal gastrectomy for stage I/II gastric cancer per year. Thus, 40 patients of enrollment will be possible within a year.

The duration of DM is a stratification factor for randimization and randon sequence is like as follow:

| **OBS** | **Duration of DM** | |
| --- | --- | --- |
|  | **>=5year** | **<5** |
| **1** | 1 | 2 |
| **2** | 2 | 1 |
| **3** | 2 | 2 |
| **4** | 1 | 1 |
| **5** | 2 | 2 |
| **6** | 1 | 1 |
| **7** | 1 | 2 |
| **8** | 2 | 1 |
| **9** | 1 | 2 |
| **10** | 2 | 1 |
| **11** | 1 | 2 |
| **12** | 2 | 1 |
| **13** | 2 | 2 |
| **14** | 1 | 1 |
| **15** | 1 | 2 |
| **16** | 2 | 1 |
| **17** | 1 | 1 |
| **18** | 2 | 2 |
| **19** | 2 | 1 |
| **20** | 1 | 2 |

1. **Study design and methods**

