**Statistical analysis**

- t-test, Chi-square test, Log-rank test, ANOVA test or Kruskal-wallis test

- HbA1c, C-peptide, lipid profile, Insulin, glucagon, IGF-1, GLP-1, Neuropeptide Y, Ghrelin, Leptin, HOMA scale: as an longitudinal data, comparing them by repeated measurement analysis of variance (RMANOVA) for comparing between Roux-en-Y gastrojejunostomy and Gastroduodenostomy

-two side p-value of less than 0.05 will be considered as statistical significance

1. Criteria for evaluation of safety, including side effects, evaluation methods and reporting methods

There are no changes in the existing surgical methods and data collection process, so there is no plan to report any postoperative complications or side effects.

1. Interim analysis

There is no planed interim analysis in this study.

1. Monitoring for data, process, and safety of this study

Investigator will do regular check.

1. Time table for the study

|  | **추진일정 (월)** | | | | | |
| --- | --- | --- | --- | --- | --- | --- |
|  | **0-1** | **2-13** | | **14-25** | **26-30** | **31-36** |
| **IRB Approval** |  |  | |  |  |  |
| **Patients’ enrollment** |  |  |  |  |  |  |
| **Data collection** |  |  |  |  |  |  |
| **Patients’ follow up** |  |  |  |  |  |  |
| **Analysis** |  |  |  |  |  |  |
| **Report** |  |  |  |  |  |  |

1. References

1) Joshua PT, David EC Cummings Hormonal and Metabolic Mechanisms of Diabetes Remission after Gastrointestinal Surgery. Endocrinology 2009 150:2518-2525

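### The sample-size justification claims 5% alpha, but its 81% power comes from a likelihood-ratio test with an actual alpha of 7.64% that the analysis section does not list

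*Protocol*

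**What the plan says.** The protocol's Sample size section assumes that remission "was around 15% after gastroduodenostomy", and that "around 57% of patients who underwent Roux-en-Y gastrojejunostomy for gastric cancer with DM experienced remission of DM". It concludes: "Thus sample size for each group will be 18 for 0.05 of alpha and 0.20 of beta". With 10% drop-out it sets the total at 40.

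The power output that follows gives one row, in the order power, N1, N2, P1, P2, D0, D1, target alpha, actual alpha, beta: "0.8091 18 18 0.5700 0.1500 0.0000 0.4200 0.0500 0.0764 0.1909". Summary Statements identifies the method: "The test statistic used is the two-sided Likelihood Ratio test". It also gives the error rate reached: "The significance level actually achieved by this design is 0.0764".

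The Statistical analysis section lists "t-test, Chi-square test, Log-rank test, ANOVA test or Kruskal-wallis test", without assigning tests to endpoints, and sets the criterion: "two side p-value of less than 0.05 will be considered as statistical significance".

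**The concern.** Three places in one document should agree and do not. The Sample size section gives alpha as 0.05. The calculation behind it achieves 0.0764. The analysis section lists a chi-square test, which is not the test used for sizing.

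Remission is the endpoint on which the trial is sized. A reader of the Sample size section would take it that false positives are held at 5% with at least 80% power. The calculation shows 80.9% power at a 7.64% false-positive rate. If the likelihood-ratio test were carried into the analysis at a nominal 0.05, that excess would come with it.

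The choice of test can also decide the result. With so few patients, some outcomes are significant by one test and not by the other, and allocation is not blinded. An unnamed test leaves room to choose after the data are seen.

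**Working it through.** **Inputs.** Remission 0.57 (Roux-en-Y) and 0.15 (gastroduodenostomy), 18 per group, alpha 0.05, beta 0.20, drop-out 10%: Sample size section. Likelihood-ratio test, power 0.8091, actual alpha 0.0764: power output and Summary Statements. Two-sided 0.05: Statistical analysis section.

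**Method.** Let x and y be the numbers in remission among n per group.
- Rejection probability = Σ Bin(x; n, p1) × Bin(y; n, p2), summed over all tables (x, y) that the test rejects. There are 19 × 19 tables for n = 18 and 21 × 21 for n = 20.
- Power: p1 = 0.57, p2 = 0.15. Size: p1 = p2 = 0.15. Maximum size: the largest value over all common rates.
- Likelihood ratio: G² = 2 Σ O ln(O/E); reject if G² ≥ 3.841.
- Pearson: X² = (x/n − y/n)² / [p(1 − p)(2/n)], with p = (x + y)/(2n); reject if X² ≥ 3.841.

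**Step 1: reproduce the protocol's figure.** Likelihood ratio, n = 18: power 0.8091, size 0.0764. Both match the output to four decimals. The maximum size is 0.0848. Ratio to nominal: 0.0764 / 0.05 = 1.53.

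**Step 2: the same enumeration for other tests.**

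| Test | Power, 36 analysed | Size at 15% (maximum) | Power, 40 analysed | Size at 15% (maximum) |
|---|---|---|---|---|
| Likelihood ratio, nominal 0.05 | 80.9% | 7.6% (8.5%) | 82.9% | 6.8% (8.5%) |
| Pearson chi-square, uncorrected | 79.4% | 4.6% (6.5%) | 82.9% | 4.9% (5.3%) |
| Boschloo exact unconditional | 77.5% | at most 5% | 80.3% | at most 5% |
| Fisher exact | 67.7% | 1.7% (2.9%) | 73.8% | 2.0% (2.5%) |
| Chi-square with Yates correction | 67.7% | 0.9% (2.9%) | 70.6% | 1.2% (2.2%) |

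If the likelihood-ratio cut-off is raised until its size at 15% is no more than 5%, power with 36 is 74.6% (size 4.6%).

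**Step 3: the shortfall under the listed test.** Uncorrected Pearson with 36: 80.0 − 79.4 = 0.6 points below the stated power, and 80.9 − 79.4 = 1.5 points below the printed power. With all 40 analysed it exceeds 80%.

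**Step 4: where the tests disagree.** With 18 per group, 3 versus 0 remissions:
- G² = 2[3 ln(3/1.5) + 15 ln(15/16.5) + 18 ln(18/16.5)] = 4.43, p = 0.035.
- X² = (3/18)² / [(3/36)(33/36)(2/18)] = 3.27, p = 0.070. Fisher p = 0.23.

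With 7 versus 2: likelihood ratio p = 0.049, Pearson p = 0.054, Fisher p = 0.12.

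**Step 5: total.** 36 / (1 − 0.10) = 40, as stated.

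**The case against.** The strongest reply has three parts.

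**The discrepancy is disclosed.** The output prints target and actual alpha side by side, defines both and repeats them in prose, and the 0.05 in the Sample size section matches the target. This is true, and the printed figures are arithmetically right. But disclosure is not reconciliation: the section that readers rely on gives only 0.05, and nothing says how the 0.0764 is to be handled.

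**The test may not differ.** A chi-square test could loosely include the likelihood-ratio chi-square, and the exact version is a detail often left to a statistical analysis plan, which may exist. That is fair as to the choice of version. It does not rescue the justification: on that reading the mismatch goes away, but the 7.64% error rate passes into the analysis.

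**The consequence is small.** This stands for the uncorrected chi-square. A shortfall of 0.6 points is minor beside two input rates that the protocol itself calls approximate.

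A reader might go further and infer that the trial cannot deliver about 80% power at 5%, or that more patients are needed. The document does not support that. The listed chi-square, uncorrected, comes within 0.6 points of 80% with 36 and passes it with 40. Insisting on 80% or more after drop-out would mean 19 per group analysed (82.1%), and 19 / 0.90 = 21.1, so 22 per group or 44 in total; a gap of 0.6 points does not call for that. The 67.7% figure would be a real loss, but it needs Yates or Fisher, and the protocol names neither.

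**Conclusion.** The sample-size justification is wrong as documented. It attributes to alpha 0.05 a power that was calculated at an actual alpha of 0.0764 (up to 8.5% over other common rates), with a test that the analysis section does not list. The problem is a mis-stated error rate and a mismatched test. It is not a materially underpowered design, and it is a matter of correction rather than a bar to the trial.

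This rests on the protocol's own rates of 57% and 15%, equal groups, and exact binomial calculation. The Pearson size of 4.6% applies at a common rate of 15%; it reaches 6.5% elsewhere with 36 patients, so the uncorrected chi-square does not strictly guarantee 5% either.

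**What to change.** - In the Sample size section and the power output, replace the likelihood-ratio calculation with one for the test that will be used on remission.
- In Statistical analysis, name that test and say whether a continuity correction applies. Do not use the likelihood-ratio test at a nominal 0.05.
- State the named test's own power and actual alpha. For the uncorrected Pearson chi-square at 57% versus 15%: 79% with 36 analysed (size 4.6% at a 15% common rate, maximum 6.5%) and 83% with 40 (4.9%, maximum 5.3%).
- If a test that guarantees 5% is preferred, state its power instead: Boschloo 78% with 36 and 80% with 40, or Fisher 68% and 74%. This is a choice for the trial team; the protocol does not require it.

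The total stays at 40. The cost is wording and a slightly less favourable power figure. The test should be fixed before remission data are analysed.

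### The protocol of this open, single-centre trial prints its own allocation list, so the next listed arm can be read before consent, and 20 slots per stratum will very probably not be enough for 40 patients

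*Protocol*

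**What the plan says.** The Protocol, under Summary Statements, says: "The duration of DM is a stratification factor for randimization and randon sequence is like as follow". The table that follows is the list itself. It has rows 1 to 20 and two columns, for diabetes of at least 5 years and of less than 5 years, with a 1 or a 2 in each cell.

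The Methods section describes the allocation as "Randomization (without blinding", with Roux-en-Y gastrojejunostomy as the experimental arm and gastroduodenostomy as the control. The section on place and period names one hospital: "Place: Severance hospital, Yonsei University College of Medicine". The Sample size section says: "sample size for each group will be 18 for 0.05 of alpha and 0.20 of beta, and estimating 10% of drop-out rate, total 40" patients are needed.

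The table gives no key for codes 1 and 2. The power summary does call group one the treatment group: "The proportion in group one (the treatment group) is assumed to be 0.1500 under the null hypothesis and 0.5700 under the alternative hypothesis". The protocol states no block size, no holder of the list, no concealment step, no cap on enrolment by stratum, and no rule for a stratum whose list is used up.

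**The concern.** The reconstruction cannot be hidden from the surgeon, so concealment of the next allocation is the main protection against selective enrolment. A list printed in the document the investigators work from removes that protection. The missing key helps little, because the first open allocation shows which code is which.

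Stratifying by diabetes duration does not remove the opportunity. Insulin use, drug treatment, HbA1c and weight are all on the protocol's list of variables and can differ between patients within a stratum. If a patient were approached, deferred or passed over in the light of the coming arm, the groups could differ before surgery in ways the analysis could not reliably repair. The trial is small: with 20 patients per arm, one patient is 1/20 = 5 percentage points of that arm's remission rate.

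The length of the list is a second, lesser problem. Twenty slots in each of two strata for 40 patients leave no margin.

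**Working it through.** **1. The plan's own sample size.** Inputs from the Protocol: 18 per group, remission 0.57 against 0.15, "The test statistic used is the two-sided Likelihood Ratio test", 10% drop-out. Exact binomial enumeration of all 19 × 19 outcomes, rejecting when the likelihood ratio statistic exceeds 1.96² (chi-square, 1 df), gives power 0.8091 and type I error 0.0764. Both match the printed line "0.8091 18 18 0.5700 0.1500 0.0000 0.4200 0.0500 0.0764 0.1909". Drop-out: 36 / (1 − 0.10) = 40, which also matches. The figure of 40 randomised patients is therefore used below. The sample size is not at issue in this point.

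**2. Reading the list in consecutive pairs** (slots 1-2, 3-4, … 19-20).

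| Stratum | Pairs | Ones / twos | Arm changes | Repeats after slot |
| --- | --- | --- | --- | --- |
| ≥5 years | 12 21 21 12 12 12 21 12 12 21 | 10 / 10 | 14 of 19 steps | 2, 6, 12, 14, 18 |
| <5 years | 21 21 21 21 21 21 21 21 12 12 | 10 / 10 | 18 of 19 steps | 16 |

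- All 20 pairs (10 per stratum) hold one 1 and one 2, as blocks of 2 would give.
- The list also fits blocks of 4. Of the 6 balanced arrangements of a block of 4, 4 have both pairs balanced, so all 10 blocks would do so with probability (4/6)^10 = 0.017. Blocks of 2 are the much likelier origin, but this is an inference.
- The <5-year column alternates strictly in slots 1-16 and again in 17-20. The ≥5-year column does not alternate.
- With the list in hand, all 40 listed slots are readable. Someone without the list who recognised the pairing could still deduce the second slot of each pair, which is 20 of 40.

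**3. Does the list suffice?** Let K be the number of patients in one stratum, K ~ Binomial(N, q). The protocol gives no value of q, so q = 0.5, 0.4 and 0.3 are assumptions. A list runs out when K > 20 or N − K > 20.

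For N = 40 the list suffices only if K = 20:

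P(K = 20) = C(40,20) × q^20 × (1 − q)^20

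- q = 0.5: 0.125, so run-out 87.5%
- q = 0.4: 0.055, so run-out 94.5%
- q = 0.3: 0.004, so run-out 99.6%

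Since q(1 − q) is largest at q = 0.5, 87.5% is the lowest run-out probability for any q. The mean number of patients beyond the list, E|K − 20|, is 2.5, 4.3 and 8.0.

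For N = 36, if only the evaluable number were randomised, the list suffices when 16 ≤ K ≤ 20. The run-out probability is then 40.5%, 66.9% and 95.3%.

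With 40 slots per stratum and N = 40, run-out is impossible.

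**The case against.** The protocol does not say who obtains consent, who assigns the arm, when in the pathway this happens, or who consults the table. A reader might infer that the operating surgeon knows the next arm and steers patients accordingly. The documents do not support that. They show that the arm can be known, not that it was known or acted upon. A concealment procedure may also exist in a document that is not shown. That part of the objection stands, and the point is worded as a risk. It does not remove the point, because a procedure elsewhere cannot conceal a list already printed in the protocol.

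Three other stronger readings also go too far.

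- The list as a whole is not strict alternation, because the ≥5-year column has five repeats.
- Blocks of 2 are not stated anywhere. Predictability from pairs alone also presupposes that staff recognise the pattern, and it adds little once the whole list is visible.
- It is not true that all 40 patients' arms are foreseeable. All 40 listed slots are, but patients beyond a used-up stratum have no listed arm.

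On run-out, the stratum shares are assumed and the result depends on how many are randomised: at 36 patients and an even split it is 40.5%, not 87.5%. A list can also be extended, so it would be too absolute to say that no valid allocation is possible. What stands is that the protocol gives no rule for that case, and that 40 is its own planned total.

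**Conclusion.** The concern holds in this limited form and should be corrected. The protocol publishes its working allocation list, in an open trial at one hospital, with no concealment step described, so the next listed arm can be read before consent from diabetes duration and order of entry alone. This follows from the text and needs no numerical assumption beyond the code key becoming apparent.

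The run-out is secondary. It rests on 40 randomised patients, no cap by stratum, and an assumed stratum share. Under those conditions its probability is at least 87.5% whatever the share.

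The documents do not show that selection bias occurred, and its size cannot be estimated from them.

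**What to change.** Remove the printed list from the protocol and discard it. Have someone independent of recruitment generate a new list, still stratified by diabetes duration, with undisclosed, randomly varying block sizes (for example 4 and 6, avoiding blocks of 2) and 40 slots per stratum. Hold it away from the enrolling surgeons, either centrally or in sequentially numbered opaque sealed envelopes, and release each allocation only after consent and registration. The protocol should describe this procedure and name the role that holds the list, without disclosing the sequence or the block sizes.

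The cost is one new list and a short amendment, with no extra patients or visits. Larger blocks may leave a slightly larger imbalance between the arms within a stratum than pairs would, which is a small price for concealment.
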